**EXPERIMENTAL INFECTION OF VOLUNTEERS WITH HEAT-STABLE TOXIN (ST)-ONLY PRODUCING ENTEROTOXIGENIC *ESCHERICHIA COLI* (ETEC): CONTRIBUTING TO THE DEVELOPMENT OF VACCINES AGAINST CHILDHOOD DIARRHEA IN LOW- AND MIDDLE-INCOME COUNTRIES.**

In 2013, we completed a study at Haukeland University Hospital where 30 volunteers were experimentally infected with a wild-type ETEC strain TW10598 which produces the thermolabile toxin (LT) as well as ST. The goal of the study was to develop an ETEC challenge model using a strain from one of the ETEC families that contribute the most to childhood diarrhea in low and middle income countries (LMIC), and to generate biological material that could be used to study immune responses and to identify potential new vaccine antigens. The study was approved by the Regional Committee for Medical and Health Research Ethics, Health Region West (REC-West, case number 2010/728-14). We consider the project a success. The strain was well tolerated by the volunteers, giving few side-effects (manuscript submitted to BMC Infectious Diseases).

As part of the newly funded GLOBVAC project “Development of a heat-stable toxoid-based (ST) vaccine for enterotoxigenic *Escherichia coli* diarrhea (ETECvac)”, we now aim to develop a challenge model that can be used for testing the efficacy of ST-based vaccines. Such models do not currently exist, but they are needed for undertaking Phase IIB clinical trials (i.e. challenge studies) of vaccine prototypes that our research consortium is currently developing. For the purpose of developing this challenge model, we wish to undertake a new experimental infection study similar to the one recently completed, but by using a new wild-type ETEC strain (TW10722) with the O115 antigen and that produces ST, but does not produce LT. In addition to evaluating the ETEC-specific humoral immune responses to the infection, like we did in our recently completed experimental infection study, we will now also evaluate cellular immune responses. Antibodies from the volunteers will further be used to screen for other ETEC antigens that have induced an immune response during the infection in order to identify new antigens that may be relevant for vaccine development. To quantitate a protective effect of an ST-based vaccine in Phase IIB trials, we will develop and test new methods to quantitate TW10722 and the amount of ST present in the stools of the volunteers. Finally, we wish to look for changes in the intestinal microbiota between before and during an ETEC infection. All studies will be conducted according to the latest version of the Declaration of Helsinki.

## **Background**

Enteric disease continues to be among the most important killers of children in LMIC. Moreover, diarrhea predisposes to malnutrition, which in turn increases susceptibility to other infections, such as pneumonia. Recent data suggest that diarrhea may also contribute to delay

in cognitive development. Over the last 20 years, case management with oral rehydration therapy and continued feeding has substantially decreased diarrhea-related deaths. However, the ~1 million deaths occurring annually still make diarrhea the second leading cause of child death (Walker *et al.*, 2007). A principal impediment to diarrheal disease control is the large number of enteropathogens. Certain diarrheal pathogens, including rotavirus, enterotoxigenic *E. coli* (ETEC), *Shigella flexnerii* and *Cryptosporidium parvum* are the most important causes of severe diarrheal disease and death (Kotloff *et al.*, 2013). Effective vaccines against ETEC, *Shigella* and *Cryptosporidium* are yet to be developed.

ETEC causes diarrhea by the release of the heat-stable toxin (ST) and/or the heat-labile toxin (LT), and they express colonization factors (CFs) which promote their attachment to the small intestinal epithelium (Walker *et al.*, 2007). Vaccine development during the last decade has mainly targeted the major CFs as well as the immunogenic LT, but they have so far failed to confer adequate protection (Walker *et al.*, 2007). ETEC strains producing only ST or both ST and LT contribute more to the disease burden in LMIC children than do those that express only LT (Levine *et al.*, 1993; Valentiner-Branth *et al.*, 2003; Kotloff *et al.*, 2013). Vaccines that induce an effective anti-ST response have not yet been successfully developed because ST is in itself non-immunogenic, and it has been difficult to render it non-toxic and at the same time immunogenic without changing its most important antigenic properties. In addition, ST has some antigenic epitopes that are similar to the human ligands guanylin and uroguanylin (Taxt *et al.* 2014), raising concerns that ST-based vaccines may also induce an immune response against these endogenous ligands. However, progress has now been made in overcoming these challenges (Taxt *et al.* 2014), and we expect that our research team can contribute to the development new ST-based vaccine prototypes, and we hope that these candidates will be ready for testing within the next few years. For this reason, there is now an urgent need to develop a human challenge model employing an ST-only ETEC strain that can be used for testing the efficacy of ST-based vaccine prototypes in coming Phase IIB trials.

## **Study objectives**

### **Overall objective**

Develop a challenge model for testing the efficacy of new ST-based vaccines

### **Specific objectives**

1. Assess the safety and identify the optimal dose for infection with strain TW10722
2. Develop new methods for quantitating strain TW10722 and ST in stools

### **Additional objectives**

3. Characterize human immune responses induced by strain TW10722

4. Screen for ETEC antigens that induce immune responses during experimental infection.
5. Characterize changes in microbiota as a result of ETEC infection

## Description of work

### 1. Assess the safety and identify the optimal dose for infection with strain TW10722

By experimentally infecting presumably immunologically naïve volunteers with wild-type ST-only ETEC strain TW10722, we will assess the safety of ingesting the strain and identify the dose that gives a 70% attack risk of diarrhea, which is suitable for use in Phase IIB trials. We will perform this dose-escalation experimental infection study similar to our previous study, starting with a low ( $1 \times 10^6$  colony-forming units [CFUs]) dosage for the first group of volunteers before gradually increasing the dosage for subsequent groups of volunteers. We expect that the optimal dose will be between  $1 \times 10^8$  and  $1 \times 10^9$  CFU, based on our and others' experiences with such studies. The maximum dosage we will attempt is  $1 \times 10^{10}$  CFU. Up to 30 volunteers will be recruited to the study. Informed consent will be collected from volunteers by researchers to which the volunteers do not have any relation of dependence. Joining the study is voluntary and the volunteer will be free to withdraw at any time.

The chosen study-strain, TW10722, was isolated from a 15-month old child suffering from diarrhea in Guinea-Bissau in 1997 (Steinsland *et al.*, 2002) and is well characterized. It has serotype O115:H5, produces the human variant of ST (STh) as well as the ETEC colonization factors Coli surface antigen 5 (CS5) and CS6, it is susceptible to most relevant antibiotics. We sequenced its entire genome in 2011 (GenBank BioProject no.: PRJNA190209). The strain is an excellent representative of an ETEC family (ETEC5) that contributes substantially to childhood diarrhea in LMIC (Steinsland *et al.*, 2010).

A working cell bank of strain TW10722 will be produced by the Inoculum Preparation Laboratory of the Center for Vaccine Development at the University of Maryland School of Medicine and shipped to Bergen on dry ice, as was done for TW105098 for our previous experimental infection study. Doses made from these culture stocks will be prepared fresh for each group of volunteers in the same manner that was performed in our previous study.

All volunteers will receive a detailed explanation of the study protocol, and on screening day they will fill out a questionnaire to ensure they have understood the information given. The screening will be performed in the outpatient clinic a few days prior to infection, where personal data and medical history will be recorded and a physical examination will be performed. The examination will include total blood cell count, measurement of serum concentrations of electrolytes, creatinine, ALT, and glucose, as well as testing for antibodies to hepatitis B and

C, and a combined antibody/antigen assay for HIV infection. Women will undergo a urine-based pregnancy test, and electrocardiograms will be taken. Stool specimens will be checked for occult blood and screened against an array of enteropathogens. The inclusion criteria will be age between 18 and 40, not having travelled to low- or middle-income countries for the previous 12 months (if this turns out to be too restrictive we may change this to 9 months), written informed consent, completed general health screening, stool culture free for enteropathogens, normal base-line blood tests, being able to be in isolation for up to 10 days, and effective contraception in the women. The exclusion criteria will be fever ( $\geq 38^{\circ}\text{C}$ ) during the last 48 hours before study initiation, allergy to ciprofloxacin or beta-lactam antibiotics, participation in other clinical trials during the last 3 months, use of immunosuppressive agent, pregnancy, breastfeeding, positive fecal occult blood test, or a history of any chronic gastrointestinal conditions.

The volunteers will be admitted to the Unit for Infectious Diseases, Department of Medicine, Haukeland University Hospital, Bergen, in cohorts of 2-4 individuals. The volunteers will fast overnight and drink sodium bicarbonate to neutralize stomach acid immediately before ingesting strain TW10722. The volunteers will be monitored in the ward for development of diarrhea and any other signs and symptoms from the gastrointestinal tract. All stools will be collected daily and cultured for the experimental ETEC strain. We will register time of evacuation, weight, and looseness of each stool that the volunteers pass. These data will be used to determine whether the volunteers got diarrhea, severity of diarrhea, incubation period, and maximum stool weight and volume during any 24-hour period. If they develop diarrhea (a single liquid stool totaling  $>200$  ml, or  $>300$  ml liquid total volume over 48 hr), they will be treated with the appropriate antibiotic drug to clear the infection within 24 hours of meeting any of these criteria or immediately if they show any signs of dehydration. In case of dehydration, oral rehydration solution, amounting to 150% of the weight of their stool, will be given at the start of diarrhea, and volunteers will be carefully monitored by a clinician (infectious disease specialist or anesthesiologist). Any volunteer who does not develop symptoms or signs within 120 hours will be treated with an appropriate antibiotic drug. For all participants, three consecutive stool samples must be verified as being negative for TW10722 prior to discharge from the hospital. Thus, the total duration of hospitalization is predicted to be  $\leq 10$  days.

The diarrhea/no diarrhea results from each new cohort will be used in a mathematical model (a beta-poisson model) designed to estimate the dose that is likely to give a 70% attack rate, and which is then given to the next cohort. The first cohort will receive  $1 \times 10^6$  CFU, and each new cohort will at most receive one  $\log_{10}$  higher dose than the previous group. If the optimal dose is found by using less than 30 volunteers, we wish to include the remaining volunteers

as a single group, all of whom will be given the estimated optimal dose. This will be done to ensure adequate statistical precision for the immunological analyses (objective 3 and 4) and we will also use the opportunity to test the quantitation method (objective 2).

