### **Potential risks or discomforts**

- Venepuncture or, if a volunteer should require intravenous (IV) rehydration (which was not required in any of the 30 volunteers in our previous study) starting an IV line may cause pain, bruising, lightheadedness, fainting, and very rarely infection. Very seldomly, bleeding may also occur from the site of venepuncture.
- The ETEC bacteria being used in this study are experimental agents. Based on previous studies with ETEC, the clinical effects that the volunteer are likely to have may include diarrhea, stomach pain/cramps, loss of appetite, headache, nausea, fever, fatigue, generalized joint and muscle aches and vomiting. Since these are experimental bacteria there is a possibility of side effects, including those that are not yet known. There is a risk of dehydration and electrolyte imbalances if diarrhea is severe. To keep the volunteer from getting dehydrated, he/she will be given fluids to drink, if clinical signs of some dehydration, we will give oral rehydration salts solution. If needed, i.e. if a volunteers shows signs or is at a risk of developing severe dehydration, fluids will be given intravenously. The volunteers will receive regular clinical examination by ward and study nurses, by study physicians and, when needed, by an anaesthesiologist.
- After ingesting the ETEC bacteria, the volunteer is likely to pass live ETEC bacteria in the stools for a few days.
- The antibiotics used to clear the ETEC infection, is usually well tolerated, but it could cause an allergic reaction (such as skin rashes, difficult breathing, or even a fatal reaction), diarrhea, nausea, and vomiting, abdominal pain/discomfort, headache, or restlessness or vaginal candidiasis (yeast infection) in women. If oral antibiotics cannot be taken, the volunteers will receive IV antibiotics.
- Although many experimental infection studies with ETEC have been undertaken during these last four decades and none have reported long term negative effects, we cannot rule out the possibility that the infection may lead to long-term sequelae, like post-infectious irritable bowel syndrome. From the three month follow-up of our previous study, there are no indications that any of our volunteers have had gastrointestinal problems after completing the study. See also external assessment with our comments in May 2010 (enclosed in REC application).

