### Schedule of study events - ETECvac - Challenge Study TW10722

| Procedure day                         | Screen      | -1        | 0 | 1 | 2 | 4 | 5 | 6 | 7     | 10     | 28       | 84      |
|---------------------------------------|-------------|-----------|---|---|---|---|---|---|-------|--------|----------|---------|
| Compliance range                      | "-60 to -1" | "-1 to 0" |   |   |   |   |   |   | "7-8" | "9-11" | "24 -30" | "70-98" |
| Outpatient visit                      | X           |           |   |   |   |   |   |   |       | X      | X        |         |
| Written informed consent              | X           |           |   |   |   |   |   |   |       |        |          |         |
| History and patient examination       | X           |           |   |   |   |   |   |   |       |        |          |         |
| Interim medical interview             |             | X (2)     | X | X | X | X | X | X | X     | X      | X        |         |
| Focused Physical examination          |             | X (2)     | X | X | X | X | X | X | X     |        |          |         |
| Blood draw                            | X           | X (2)     |   |   |   |   |   |   | X     | X      | X        |         |
| Screening lab tests (3)               | X           |           |   |   |   |   |   |   |       |        |          |         |
| Hematology and Chemistry (4)          | X           |           |   |   |   |   |   |   |       | X      |          |         |
| HCG urine                             | X           | X (2)     |   |   |   |   |   |   |       |        | X        |         |
| Inpatient stay                        |             | X         | X | X | X | X | X | X | X     |        |          |         |
| Challenge                             |             |           | X |   |   |   |   |   |       |        |          |         |
| Stool collection/cultures             | X (5)       |           | X | X | X | X | X | X | X     | X      |          |         |
| Stool weighing/Grading                |             |           | X | X | X | X | X | X | X     |        |          |         |
| Stool bacteriology (strain detection) |             |           | X | X | X | X | X | X | X     |        |          |         |
| PBMCs for immunological assays        |             | X (2)     |   |   |   |   |   |   | X     | X      | X        |         |

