## **Relevant amendments to protocol August 2016**

### **New ST-only challenge strain**

ETEC bacterial strain used in the study was changed from TW10722 to TW11681.

Rationale: After performing a dose-escalation study in the fall of 2014, where we infected 3 groups of 3 volunteers with respectively  $1 \times 10^6$ ,  $1 \times 10^7$ , and  $1 \times 10^8$  colony forming units of strain TW10722, few of the volunteers appeared to actually become colonized with the strain, and only one volunteer became ill and developed (severe) diarrhea.

For the next groups of volunteers, we wish to repeat dose escalation experiments with wild-type ETEC strain TW11681 (O19:H45; STh-CFA/I CS21), which belong to the epidemiologically relevant ETEC8 family. Results from phylogenetic and comparative genomics analyses of TW11681 and 19 other ETEC8 strains suggest that TW11681 is a good representative for ETEC8. Also, TW11681 is sensitive for the antibiotic we use (Ciprofloxacin), and does not seem to have any potential dangerous traits other than the ability to cause diarrhea.

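### The written escalation rule takes diarrhea yes/no as its only outcome, so nothing in it holds or lowers the next dose after a severe non-diarrheal reaction

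*Supplement*

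**What the plan says.** The dose rule is under Description of work, item 1 (safety and optimal dose). It reads "The diarrhea/no diarrhea results from each new cohort will be used in a mathematical model (a beta-poisson model) designed to estimate the dose" likely to give a 70% attack rate, "which is then given to the next cohort". Diarrhea is defined by liquid stool alone: one stool above 200 ml, or more than 300 ml in total over 48 hours.

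Two limits apply. The step is capped, "and each new cohort will at most receive one" log10 above the one before. There is also a ceiling: "The maximum dosage we will attempt is" 1×10^10 CFU.

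Safety shares specific objective 1 with dose finding. Potential risks or discomforts lists, among the likely effects, "headache, nausea, fever, fatigue, generalized joint and muscle aches and vomiting", and adds that "there is a possibility of side effects, including those that are not yet known". The Schedule of study events puts an "Interim medical interview" and a focused physical examination on seven listed days from Day 0 to Day 7 (0, 1, 2, 4, 5, 6, 7).

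The August 2016 amendment reports TW10722 given in 2014 to three volunteers each at 1×10^6, 1×10^7 and 1×10^8 CFU, of whom "only one volunteer became ill and developed (severe) diarrhea". The April 2017 amendment returns to TW10722 at higher doses, after TW11681 seemed to cause mainly non-diarrheal symptoms in nine volunteers.

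**The concern.** The protocol collects tolerability data and makes safety an objective, but no written step carries those data into the decision on the next dose. The antibiotic and rehydration rules protect the volunteer already dosed and do not govern the next cohort.

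A volunteer with high fever or repeated vomiting, but too little liquid stool, counts in the fit as a non-event. If nobody in the cohort has diarrhea, the fit treats the dose as too low and asks for more. The next cohort could then receive up to ten times a dose that had just made people ill.

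This applies to the current version. TW10722 is now to be given above the 1×10^8 CFU reached in 2014, and the text shown holds no tolerability data for the strain there. Experience with TW11681 shows, for another strain, that illness and the modelled endpoint can come apart.

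**Working it through.** The plan gives no figure to reproduce. The check has three parts.

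**1. What the written rule responds to.**
- Model input: diarrhea yes/no. Responds to stool volume only.
- Step cap of one log10: fixed, responds to no outcome.
- Ceiling of 1×10^10 CFU: fixed, responds to no outcome.
- Scheduled interviews and examinations: recorded, but not linked to escalation anywhere in the text shown.

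**2. What the rule does after a cohort with no diarrhea (illustration).**

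Inputs from the documents: 3 volunteers each at 1×10^6, 1×10^7 and 1×10^8 CFU with one case; cohorts of n = 2 to 4; the step cap; the ceiling. Assumed: the dose at which the one case occurred (not stated, so each of the three is tried) and the lower bound on the shape parameter α, which the plan does not give and one case in nine cannot identify (0.05, 0.1, 0.2, 0.5, 1 and a near-exponential limit). That makes 6 × 3 × 3 = 54 settings.

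Model: P(d) = 1 − [1 + (d/N50)(2^(1/α) − 1)]^(−α), fitted by maximum likelihood. The 70% dose is D70 = N50 (0.3^(−1/α) − 1)/(2^(1/α) − 1).
- First step: d1 = min(D70, 1×10^9), giving 3.4×10^8 to 1×10^9 CFU.
- Add 0/n with diarrhea at d1 and refit: d2 = min(D70, 10·d1, 1×10^10).
- Result: d2/d1 lies between 3.4 and 10 in all 54 settings, with d2 from 1.2×10^9 to 1×10^10 CFU.

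Hand check of the smallest step, in the exponential limit P = 1 − exp(−r·d), case at 1×10^6. The doses of the eight volunteers without diarrhea sum to S = 2×10^6 + 3×10^7 + 3×10^8 = 3.32×10^8, and r ≈ 1/S. So D70 = −ln(0.3)·S = 1.204 × 3.32×10^8 = 4.0×10^8. Adding n volunteers without diarrhea at that dose multiplies S, and hence D70, by 1 + 1.204n: 3.41, 4.61 and 5.82 for n = 2, 3, 4.

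The push is not general. If 3 of 4 have diarrhea at d1 and the fourth is ill without it, the next dose falls to 0.86 to 0.90 of d1 in 12 of 18 settings. With 2 of 3 it is nearly flat, about 1.06 to 1.08 times d1, in 12 of 18. The other six (α floors of 0.2 or less, case at 1×10^6 or 1×10^7) still rise.

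These fits show direction only. They do not measure harm: a cohort without diarrhea raises the estimate whether or not anyone was ill, and the fix leaves the model unchanged.

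**3. How often a hold would be triggered.**

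For a true risk p of a severe related non-diarrheal reaction (assumed), the chance of at least one in a cohort is 1 − (1 − p)^n, and of two or more it is 1 − (1 − p)^n − np(1 − p)^(n−1).

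| p | at least one, n = 2, 3, 4 | two or more, n = 2, 3, 4 |
|---|---|---|
| 5% | 10%, 14%, 19% | 0.3%, 0.7%, 1.4% |
| 10% | 19%, 27%, 34% | 1.0%, 2.8%, 5.2% |
| 30% | 51%, 66%, 76% | 9%, 22%, 35% |

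Example, p = 10%, n = 3: 1 − 0.9^3 = 0.271; less 3 × 0.1 × 0.81 = 0.243 leaves 0.028.

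**The case against.** A reader might infer that a severe reaction cannot hold the next dose. The documents do not support that. The step limit and the ceiling are upper bounds, nothing obliges the team to dose another cohort, and nothing forbids a pause. The study's history also points to judgement. In 2014 the TW10722 escalation ended at 1×10^8 CFU with one case in nine, where a mechanical rule would have gone higher, and TW11681 was dropped with non-diarrheal symptoms in view. This stands against the word cannot. It does not supply a hold rule: the reasons given were few volunteers colonized and little diarrhea in one case, and unsuitability as a challenge strain in the other, not safety.

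A rule may also exist elsewhere. The protocol models the escalation on the previous study and refers to an external assessment enclosed with the ethics application. Parts of the supplement were not available either. This limits confidence. If such a rule exists, a cross-reference beside the dose rule is enough.

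Other restraints are real: cohorts of 2 to 4, inpatient care, specialist cover, antibiotics, the step cap and the ceiling. They limit exposure, but do not tie the next dose to how the last cohort fared.

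Finally, it can be said that the arithmetic shows no harm and that no reaction rate is known for TW10722. Both are correct. The point rests on what the rule leaves out, not on a frequency.

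**Conclusion.** The point holds for the text shown: nothing in the written rule holds or lowers the next dose after a severe non-diarrheal reaction, and such a volunteer without a qualifying stool is scored as a non-event. After a cohort with no diarrhea, following the rule means a 3.4- to 10-fold higher dose in every setting tried. The direction is robust; the exact dose depends on the assumed α bound and on where the one 2014 case is placed.

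Two stronger readings should be resisted. Such reactions do not always push the dose up, since in cohorts where most have diarrhea the next dose may fall or stay level. Nor is TW10722 known to cause illness without diarrhea: none is reported up to 1×10^8 CFU, and the TW11681 symptoms are another strain's, with no severity stated.

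The change should be made, because volunteers would be safer at small cost. Confidence is medium, since a rule in unseen text is possible and clinicians may well step in without one. Unwritten discretion, however, could differ from cohort to cohort.

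**What to change.** After the one-log10 limit in Description of work, item 1, add wording to this effect:

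*The model estimate is an upper limit for the next dose. Before each new cohort, including the final single group, the study physicians review the non-diarrheal effects recorded in the last cohort up to discharge. An effect is severe if it prevents normal activity or needs medical intervention. If one volunteer had a severe non-diarrheal effect judged related to the challenge, the next cohort's dose does not exceed that cohort's dose. If two or more did, the dose is lowered or escalation stops. The decision is documented.*

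The beta-Poisson input stays diarrhea yes/no, so the attack-rate estimate keeps its meaning. Reviewing up to discharge means that the next cohort need not wait for the Day 28 interview.

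The cost is one paragraph and a short documented review by physicians already on the study, using data already scheduled. No visit, procedure or staff is added. The downside is that some doses would be held or repeated, in 10% to 19% of cohorts at an assumed 5% risk and 19% to 34% at 10%. Each repeat uses 2 to 4 of at most 30 volunteers, and the 70% dose might not be reached.
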